## Background

Today, it is widely acknowledged that the onset and development of chronic pain syndromes is a result of complex interactions between biological, psychological and social influences, including patients’ beliefs about their self-efficacy, hypervigilant monitoring of bodily sensations, familial conflict or social support [19, 21, 22, 32]. If patients, for example, exhibit maladaptive behavioral or cognitive responses to acute episodes of pain, the pain may become chronic, thus affecting the long-term course [41].

Attachment theory provides a useful framework to classify patients’ relatively stable cognitive, emotional and behavioral response styles to stressors (such as pain), which have been successfully linked to disease processes in general [24, 35] and to diagnosis and processes of pain-related diseases in particular [37, 43]. Based on their dominant response patterns, adults can be classified to one of four attachment styles - one *secure* style, and the three insecure styles *dismissing*, *preoccupied*, and *fearful* [2, 38]. Bartholomew and Horowitz developed a model based on these four attachment styles (for a simplified overview, see Fig. 1). This model shows that adults with a secure style see themselves and others in a positive way, whereas fearful adults tend to see themselves and others in a negative way [2].

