## Methods

### Design

The study is conducted in a block design with two patient groups as blocks (baseline, attachment intervention) and 3 assessments T1, T2, and T3 (before treatment, post-treatment, and at a 6 month follow-up). We decided against a randomized controlled trial because (a) we had ethical concerns with a design that would put patients on a waiting list for several months, and (b) a block design ensures that the intervention’s effects only influence the outcomes of the treatment group: After collection of data for the control group, the health care personnel of the outpatient pain clinic receives training sessions on attachment theory and its use in the therapeutic context. These training sessions will not be carried out until data collection for the control group will be complete. More attachment-related training sessions alternating with supervision meetings will be held on a monthly basis to assist the therapeutic team in the practical application during data collection for the second sample, the treatment group. During our weekly team meetings, the case reviews will be complemented with a discussion on the individual attachment style of each patient. Also these meetings will be used to collect situations, which are perceived to be critical for the forming of a working alliance by the therapeutic team (for example, situations in which the patient misses entire therapeutic sessions or appears too late to them on a regular basis). These critical situations will be subsequently used to structure the discussions of individual cases in the bi-monthly training sessions.

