### Statistical analysis

Descriptive statistics will be used to describe the characteristics of the study sample. Analysis of variance will be used for the evaluation of the changes of the continuous outcomes pain intensity and physical functioning (T1-T2, T1- T3). Research condition (attachment style and study group), will be used as independent variable. Demographic variables such as sex, age, education and clinical variables such as opioid intake and comorbidity will be entered as covariates. Partial regression coefficients will be used to determine if the “working alliance” mediates the effect of attachment on the continuous outcomes (pain and physical functioning).

Missing data on the questionnaires will be handled according to the questionnaire protocol.

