#### Demographic information, help-seeking behavior and use of medication

Items are adapted from the German Pain Questionnaire. The German pain questionnaire (DSF; [42]) has been developed and validated by the International Association for the Study of Pain (DGSS). The concept of the DSF is based on a bio - psycho - social pain model. The modular approach to pain assessment consists of: demographic data, pain variables (e. g. pain sites, temporal characteristics, duration, intensity), pain associated symptoms, affective and sensory qualities of pain (adjective list by Geissner, SES Copyright, [23]), pain relieving and intensifying factors, previous pain treatment procedures, pain-related disability (Pain Disability Index by [49]), depression test CES-D (Center for Epidemiological Studies Depression Test), comorbid conditions, social factors (educational level, occupation, retirement status, compensation and/or litigation status, disability for work),health related quality of life (SF-36 Copyright).

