#### Attachment style

Assessments of both intervention group and baseline group are identical. For an overview of all measures at T1, T2, and T3, see Table 1. Patients’ attachment patterns will be assessed with the help of the relationship questionnaire (RQ 2; [2]) and the revised Experience of Close Relationships questionnaire [15] in its newly developed German short version [6, 15] . The ECR-RD 12 has been anchored in two different ways to assess the two regulatory attachment strategies *avoidance* and *anxiety* (a) specifically with regard to partners or spouses and (b) more globally with regard to friends and relatives. The original version of the ECR-R [20] was based on the principles of item response theory and specifically assesses attachment representations in romantic relationships (e.g. attachment anxiety: ‘I find that my partner/partners doesn’t/don’t want to get as close as I would like’; attachment avoidance: ‘I find it difficult to allow myself to depend on romantic partners’).

**Table 1 Tab1:** Overview of variables and instruments

Domain	Instruments	T1	T2	T3
Psychological disorders, axis 1	*German semi-structured Clinical Interview* based on DSM-IV (SKID-I)	**×**		
Socio-demographic variables	Items adapted from the *German Pain Questionnaire*	**×**		
Help-seeking behavior	Items adapted from the *German Pain Questionnaire*	**×**		**×**
Use of Medication	Items adapted from the *German Pain Questionnaire*	**×**		**×**
Attachment Patterns	•* Relationship Questionnaire* (RQ 2) •* Experience of Close Relationships* (ECR-RD 12) with regard to a) partner/spouse b) friends/relatives	**×**		**×**
Pain	•* Pain Intensity* **:** Visual Analogue Scales (VAS) • *Pain Frequency*: number of days with pain, number of days with strong pain (previous month)	**×**	**×**	**×**
Physical Functioning	• *Oswestry Disability Index* (ODI) •* Health Survey* (SF12)	**×**	**×**	**×**
Emotional Distress	•* Depression, Anxiety and Stress Scale* (DASS) •* Health Survey* (SF12)	**×**	**×**	**×**
Interpersonal Problems	*Inventory of Interpersonal Problems* (IIP 32)	**×**	**×**	**×**
Self-esteem	*Rosenberg Self Esteem Scale* (RSES)	**×**	**×**	**×**
Coping	*Coping Strategies Questionnaire* (CSQ-D)	**×**	**×**	**×**
Evaluation of Therapeutic Process	•* Working Alliance Inventory* (WAI) •* Therapie Stations-Erfahrungs-Bogen* (TSEB)		**×**	

*T1, before treatment; T2, after treatment; T3, six months follow-up*

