## Conclusions

### Trial status

Recruitment of patients for the control group started in March 2012. Pre- and post-treatment assessments were complete by Oct. 2013 with a total of 184 patients who received a questionnaire at T1 (for an overview of the recruitment process including dropout numbers, see Fig. 3). The 6-month follow-up questionnaires of the control group were completely sent out by May 2014. Each team member received monthly intervention training sessions between Nov. 2013 and May 2015. For an overview of the received attachment training, see Table 2. Recruitment of patients for the intervention group started in March 2014. Pre- and post-tretments were complte by Dec. 2015 with a total of 194 patients who received T1. The 6-months follow-up questionnaires of the interventions group will be completely sent out by June 2016.

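### The adjustment set for two sequential, non-randomised blocks does not name the T1 distress, coping, interpersonal-problem and self-esteem scores that are collected in both blocks

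*Protocol article*

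**What the plan says.** The Design section sets out consecutive groups: "The study is conducted in a block design with two patient groups as blocks (baseline, attachment intervention". It adds: "We decided against a randomized controlled trial". The reasons given are waiting times and keeping the intervention out of the control group; neither concerns case mix. Under Trial status, "Recruitment of patients for the control group started in March 2012", with pre- and post-treatment assessments complete by October 2013. Intervention recruitment started in March 2014, and its pre- and post-treatment assessments were complete by December 2015.

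The Statistical analysis section applies analysis of variance to change in pain intensity and physical functioning (T1-T2 and T1-T3), with attachment style and study group as independent variables. On adjustment it says: "Demographic variables such as sex, age, education and clinical variables such as opioid intake and comorbidity will be entered as covariates". The article describes no matching, weighting or other control for differences between blocks.

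Table 1 lists the "Depression, Anxiety and Stress Scale", the Coping Strategies Questionnaire, the Inventory of Interpersonal Problems and the Rosenberg scale at T1, T2 and T3, and the text introducing the table says that assessments are identical in the two groups. The Background attributes the onset and development of chronic pain to "complex interactions between biological, psychological and social influences".

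**The concern.** In a randomised trial, leaving a prognostic baseline score out of the model costs some precision. Here it can cost validity. If patients in the second block arrived with less distress or better coping than those in the first, and such patients improve more under any treatment, that difference goes into the study-group coefficient. It does not shrink as the sample grows, whereas the standard error does, so the false-positive rate rises with sample size.

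The article's own account of chronic pain gives psychological and social factors a leading role, and four such measures are taken at T1 in both blocks. The covariates that it names are three demographic items, opioid intake and comorbidity.

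Adjusting for T1 pain alone would not close the gap: two patients with the same T1 pain but different distress or coping may be expected to change differently.

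**Working it through.** The plan states no figure for block imbalance or for the prognostic strength of any T1 score, so there is nothing to reproduce. What follows is a sensitivity illustration.

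**Inputs from the article:** 93 per group, two-sided alpha 0.05 and planned effect 0.4 SD (Sample size calculation).

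**Assumptions, not in the article:** four unadjusted T1 scores with pairwise correlation 0.3 and equal slopes b; joint R² of 0.10 or 0.20 for change; every score shifted between blocks by the same d in the same direction; no overlap with the named covariates or attachment style; true effect zero; SD of change set to 1.

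**Step 1, slope.** R² = b² × (4 + 12 × 0.3) = 7.6 b².
- R² = 0.10: b = √(0.10/7.6) = 0.115
- R² = 0.20: b = √(0.20/7.6) = 0.162

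**Step 2, bias.** Bias = 4 × b × d, which is 0.459 d or 0.649 d.

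**Step 3, type I error.** SE = √(2/93) = 0.147. Error = 1 − Φ(1.96 − bias/SE) + Φ(−1.96 − bias/SE).

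| d (SD) | R² | Bias (SD) | Share of 0.4 | Type I error |
|---|---|---|---|---|
| 0.1 | 0.10 | 0.046 | 11% | 6.1% |
| 0.1 | 0.20 | 0.065 | 16% | 7.3% |
| 0.2 | 0.10 | 0.092 | 23% | 9.6% |
| 0.2 | 0.20 | 0.130 | 32% | 14.3% |
| 0.3 | 0.10 | 0.138 | 34% | 15.5% |
| 0.3 | 0.20 | 0.195 | 49% | 26.4% |

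**Step 4, how far milder assumptions reduce this.** If the named covariates and attachment style absorb half of the bias, the d = 0.2 rows fall to 0.046 and 0.065 SD, with errors of 6.1% and 7.3%. If two scores shift up and two shift down by the same amount, the biases cancel to zero.

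**Step 5, the T1 outcome.** Analysing change does not remove a T1 imbalance in the outcome itself. Take T1 pain differing by 0.3 SD, correlation r between T1 and the later value, and equal SDs. Regression to the mean then gives a spurious difference of (1 − r) × 0.3 outcome SD, against an SD of change of √(2(1 − r)). At r = 0.5 this is 0.15 with an SD of change of 1, and the error at 93 per group is 17.6%. It is 22.7% at r = 0.3 and 12.4% at r = 0.7. The T1 outcome value therefore belongs in the same set.

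**The case against.** Several points on the other side stand.

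- **The list is illustrative.** It is worded as examples, so the T1 scores are unnamed, not excluded. A reader might infer that the plan rules them out, or that the open wording is itself a defect. The documents support neither: a condensed article may leave the final list to the analysis plan. What remains is that the article gives its leading covariates and omits those which its own Background makes most relevant.
- **Part of the gap is already covered.** Attachment style is in the model, and the Background ties insecure attachment to poorer coping, depression, anxiety and lower self-esteem. Comorbidity may include the SCID-I diagnoses taken at T1. Neither is a substitute for dimensional scores, but both would reduce the bias.
- **Prognostic value is not demonstrated.** A reader might take the Background to show that catastrophising, depression and anxiety predict the course of pain. That text presents them as correlates of insecure attachment. Only the general biopsychosocial statement supports a prognostic role, and it does not show that any one score predicts change in this programme.
- **Work and compensation items may not exist.** The Measures section mentions "social factors (educational level, occupation, retirement status, compensation and/or litigation status, disability for work", but there it describes the parent German Pain Questionnaire, from which items were adapted. Table 1 says only that socio-demographic variables are collected, so these items cannot be assumed to be on file.
- **The illustration leans upward.** It uses same-direction shifts and gives no credit for overlap. Using the 184 and 194 patients under Trial status would raise the error rates, but those are patients who received a T1 questionnaire, not patients analysed.

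**Conclusion.** The point holds in a limited form. The comparison is not randomised, covariate adjustment is the only protection against case-mix differences that the article describes, and four T1 psychological scores available in both blocks are not among the named adjusters. A block difference in them, beyond what attachment style and the five named covariates capture, would bias the study-group effect.

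The documents do not give the size, and nothing in them shows that the blocks do differ. Under the stated assumptions the bias runs from 0.05 to 0.19 SD, roughly a tenth to a half of the planned effect, with a type I error of 6 to 26% at 93 per group. The lower end is minor, and overlap or opposing shifts would move the true position towards it. The case for the change rests on its low cost in a design with little other protection, not on any one figure in the table.

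**What to change.** In the Statistical analysis section, keep attachment style and the five named covariates. Add T1 DASS, CSQ-D, IIP 32 and RSES, together with the T1 value of the outcome analysed (VAS or ODI). State that this is one fixed set for the study-group contrasts at T1-T2 and T1-T3. Report standardised T1 differences between the blocks for every variable in it.

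- Add work, retirement or compensation items only if they were in fact collected.
- Propensity (overlap) weighting on the same T1 variables may be an optional sensitivity analysis.
- For the separate hypothesis about attachment style itself, report the model without the added psychological scores, since they may lie on the pathway from attachment to outcome.
- Record when the set was fixed. Pre- and post-treatment assessments were complete in both blocks by December 2015, so fixing it before the last follow-up forms return does not by itself show that the T1-T2 analysis was specified without sight of the data.

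The cost is a few degrees of freedom against a planned 186 patients, and a rule for missing T1 items. No new data collection is needed for the four scores. Adjustment deals with measured case mix only: changes at the clinic or in referral between 2012-13 and 2014-15 stay inseparable from the intervention, and the report should say so.

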Attachment-based Working Alliance Model

Patients in the intervention group, who receive an attachment-based multidisciplinary treatment, will report a larger mean reduction of the pain intensity between pre-treatment and post-treatment assessments than patients in the control group, who receive the state-of-the-art multidisciplinary treatment. It is expected that this larger reduction of the pain intensity in the intervention group compared to controls can be specifically attributed to better outcomes for the intervention group patients than control group patients who have been assessed with insecure attachment styles. Moreover, patients with an insecure attachment style and patients with more attachment anxiety are expected to report higher levels of pain intensity as well as physical functioning.The intervention is specifically designed to improve the therapeutic relationship and to hereby improve treatment outcomes. Therefore, we expect to find improved ratings of the relationship (working alliance) between patients and therapists in the intervention group which will mediate the treatment outcomes pain intensity and physical functioning.There will be a greater decline in help-seeking behavior and use of medication in the intervention group compared to the control group from pre-treatment to after the 6-month follow-up. This will be especially hypothesized for insecurely attached patients in the intervention group.Subjective self-awareness of the patients particularly with regard to self-esteem will be expected to change to a greater extent in the intervention group compared to the control group.

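### The mediation analysis names attachment as the exposure, whereas the hypothesis is that working alliance mediates the effect of the intervention, so the hypothesised path is not tested

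*Protocol article*

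**What the plan says.** The hypotheses at the end of the Background (after Fig. 2) give the rationale: "The intervention is specifically designed to improve the therapeutic relationship and to hereby improve treatment outcomes". They then expect better alliance ratings "in the intervention group which will mediate the treatment outcomes pain intensity and physical functioning". The Intervention section likewise presents a better therapeutic alliance as what the training is meant to achieve.

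Statistical analysis describes one mediation analysis. It begins "Partial regression coefficients will be used to determine if the" working alliance "mediates the effect of attachment on the continuous outcomes (pain and physical functioning". Earlier in the same paragraph, for the analysis of variance, it says: "Research condition (attachment style and study group), will be used as independent variable". The outcome changes named there are T1-T2 and T1-T3. The article does not say which of them the mediation model uses.

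In Table 1 the row "Evaluation of Therapeutic Process" (WAI and TSEB) is marked at T2 only, while pain and physical functioning are marked at all three assessments. The footnote defines these as "T1, before treatment; T2, after treatment; T3, six months follow-up".

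**The concern.** The hypothesis and the analysis have the same mediator and the same outcomes but different exposures. The hypothesis is about what the training does. The analysis is about a characteristic that patients bring with them.

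Two errors can follow. A real effect of the training through alliance could go unreported because no stated analysis looks for it. Or a finding that insecure patients form weaker alliances and do worse could be presented as support for the mechanism of the intervention, on which it has no bearing.

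Timing adds a smaller problem. With alliance rated at the assessment that also gives the T2 outcome, a model for the T1-T2 change cannot separate alliance improving the outcome from a good outcome improving the rating. Naming the right exposure does not remove this.

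**Working it through.** The article gives no figure to reproduce for this point. The check sets the texts side by side and then illustrates the consequences. Every path size below is an assumption; 93 per group (186 in total) and the 0.4 SD effect come from Sample size calculation.

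**1. The texts compared**

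| | Exposure | Mediator | Outcome |
|---|---|---|---|
| Hypothesis (Background) | study group | working alliance | pain intensity, physical functioning |
| Statistical analysis | attachment | working alliance | pain, physical functioning |

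**2. What the mismatch does.** Linear model, 186 patients, 60% insecure (assumed), 4,000 replicates, higher outcome = worse. Mediation is declared when both the exposure-to-alliance path (a) and the alliance-to-outcome path (b) have p < 0.05. The indirect effect is a × b.

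- Alliance carries only the group effect, a = 0.5 SD, b = -0.4: true group indirect effect 0.5 × (-0.4) = -0.20. The group test detects it in 92% of replicates. The attachment test is positive in 5%, with a mean indirect effect of 0.00.
- Alliance carries only the attachment effect, a = -0.5 SD, b = -0.4: true attachment indirect effect (-0.5) × (-0.4) = 0.20. The attachment test is positive in 91%, while the group indirect effect is zero.

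**3. What the T2 timing does once study group is the exposure.** Suppose the training improves the T2 outcome by 0.4 SD with no path through alliance, and alliance merely reflects improvement with correlation c. Path a is then 0.4c and path b is c, so the spurious indirect effect is 0.4c².

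| c (assumed) | Spurious a × b | Share of the 0.4 effect | Both paths significant |
|---|---|---|---|
| 0.2 | 0.016 | 4% | about 6% |
| 0.3 | 0.036 | 9% | about 13% |
| 0.4 | 0.064 | 16% | about 20% |

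The last column is simulated. A variant with alliance noise of 1 SD at c = 0.4 gave 18%, so the last entry is good to a couple of points.

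**4. Which T3 model to use.** Suppose true mediation occurs during treatment: group to alliance 0.5, alliance to T2 outcome 0.4, T2 to T3 outcome 0.6, no later direct path. The effect of the training on T3 through alliance is 0.5 × 0.4 × 0.6 = 0.12.

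- T3 adjusted for T1 only: mean indirect effect 0.12, detected in about 85% of trials.
- T3 adjusted for T2 as well: mean indirect effect about 0.00, detected in about 5%, because T2 lies on the path.

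The 85% can be checked by hand with outcome variances scaled to 1. Path b is 0.4 × 0.6 = 0.24, with residual variance 0.36 × 0.84 + 0.64 = 0.94, so z = 0.24 / √(0.94/186) = 3.4. Path a has z = 0.5 / (2/√186) = 3.4. Each path then has power of about 0.92, and 0.92 × 0.92 = 0.85. Noisier outcomes lower this rate but leave the contrast between the two models in place.

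**The case against.** The best defence is that "attachment" in the mediation sentence is shorthand for the attachment intervention, a label the article does use for the second block. That is possible but weak: the same paragraph treats attachment style and study group as two variables. Even on that reading, the exposure of a stated hypothesis is ambiguous and needs one clarifying word.

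A second defence is that attachment as exposure is a sensible question, since the Background reports that insecurity harms both alliance and outcome. This stands. That model is worth keeping, but it answers a different question.

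Three stronger readings are tempting, and the article does not support them.

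- A reader might infer that the plan would declare false mediation in nearly every trial, because under the reverse correlations above the alliance coefficient alone is significant in 77% to 100% of simulated trials. That is only the power to find a correlation built into the simulation. Mediation also needs path a, and requiring both gives the 6% to 20% shown.
- A reader might infer that the plan tests only the alliance coefficient. The article speaks of coefficients in the plural, which is compatible with estimating both paths. How the indirect effect is tested, by bootstrap or otherwise, is detail that a condensed article may leave to the analysis plan.
- A reader might infer that the single alliance rating invalidates any mediation analysis. It does not: T1-T3 is also a named contrast, and there the rating precedes the final outcome.

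**Conclusion.** The point holds in this form: the mediation analysis as written does not test the mediation hypothesis as written, because its exposure is attachment and not study group. This rests on the text alone and does not depend on any simulation.

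The simulations show only how the mismatch could matter. The hypothesised path can be missed almost entirely (5% flagged against 92% detectable), or an attachment result can be taken for it (91% positive with no group indirect effect). The rates depend on the assumed paths. The timing problem is secondary, applies only to the T1-T2 outcome, and is of moderate size under the assumed reverse correlations.

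This should be fixed, but it is not critical. The primary comparisons of pain and functioning, the analysis of variance with study group as a factor, and the sample size are untouched.

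**What to change.** Amend the mediation sentence in Statistical analysis to say:

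- The exposure is study group (intervention versus control), the mediator is working alliance at T2, and the outcomes are pain intensity and physical functioning. Mediation is claimed only if both the group-to-alliance and the alliance-to-outcome paths are supported. The covariates already listed (sex, age, education, opioid intake, comorbidity) enter both models.
- The main mediation model uses the T3 outcome adjusted for its T1 value. It does not adjust for the T2 value.
- The T1-T2 mediation model is also reported, labelled cross-sectional, with the caution that improvement may raise the alliance rating.
- Attachment style may enter as a moderator. The model with attachment as exposure may stay as a secondary analysis.

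The cost is one reworded sentence and one further model on measurements already in the schedule. The T3 model will lose patients to follow-up; the article's text does not give the size of that loss. Because the groups are sequential and not randomised, both paths stay open to confounding whichever outcome is used, and the report should say so.

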### Intervention

By drawing on attachment theoretical ideas, we do not mean to change any of the overall aims of multimodal pain treatment. Also, it would be unrealistic to aim at a complete reversal of underlying insecure attachment patterns to a secure pattern in such a setting.

Rather, we aim at an improvement of the therapeutic alliance (a) in terms of the therapists’ general ability to provide a secure base for his patients, and (b) in the therapists’ ability to understand and deal with their patients’ individual attachment-based motivations and needs. Thus, the intervention’s guidelines should help facilitate the attainment of the program’s aims by enhancing the patient’s sense of having a secure base. Therefore, our intervention training includes both general directions for building a meaningful therapeutic relationship, and guidelines, which are specifically tailored to the needs of individual attachment styles.

To develop general guidelines for an improvement of the working alliance, we identified as useful starting point the therapeutic approach of the complementary therapeutic relationship. This approach emphasizes the underlying motives (such as the attachment motive) of patients [9, 48].

We also developed more specific guidelines for each attachment style based on a further development of existing literature on the application of attachment ideas to specific therapeutic settings. For example, attachment theoretical ideas have been incorporated in therapeutic programs for the treatment of borderline personality disorder, depression, medically unexplained symptoms, family and couple therapy [3, 13, 25, 28, 29]. A multimodal rehabilitation program for children and adolescents with functional impairment in Australia applies for instance attachment principles to their family-based intervention [29, 30]. However, as guidelines often remain vague, are tailored to one specific therapeutic school or are given on the assumption of a long-term therapy, all of which is not suitable for our context, we only used them as a starting point.

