The short time frame of this setting, which is already packed with activity, might simply not be enough to adequately absorb these experiences and to tap into them in a therapeutic sense. Therefore, the setting in itself could be unsuited to a treatment concept which is individually tailored to specific attachment styles. It might even be unsuited altogether for patients who are known to have difficulty to become self-dependent once the intense support they receive throughout the program discontinues. On the other hand, as such an individually tailored attachment concept has never been applied to multimodal pain treatment and attachment styles clearly are very relevant in this setting, there is also the chance that treatment can be largely improved. Moreover, we do not aim at altering the individual attachment patterns of the patients themselves. Rather, we use the knowledge about these patterns to form an adequate basis from which we can start working with the patients on their pain related goals without overstraining them.

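### The mediation analysis names the patient's attachment as the exposure, whereas the hypothesised mechanism runs from study group through the working alliance

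*Protocol article*

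**What the plan says.** The hypotheses (Background, text after Fig. 2) give the purpose of the programme: "The intervention is specifically designed to improve the therapeutic relationship and to hereby improve treatment outcomes". They go on to expect improved ratings of the relationship "between patients and therapists in the intervention group which will mediate the treatment outcomes pain intensity and physical functioning". The chain is study group, then working alliance, then outcome.

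The section Statistical analysis has one sentence on mediation. It relies on partial regression coefficients to judge whether the alliance "mediates the effect of attachment on the continuous outcomes (pain and physical functioning". Two sentences earlier, for the analysis of variance, it states: "Research condition (attachment style and study group), will be used as independent variable".

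On whether attachment is something the treatment changes, the section Intervention says that "it would be unrealistic to aim at a complete reversal of underlying insecure attachment patterns" to a secure pattern in this setting, and Potential limitations says that "we do not aim at altering the individual attachment patterns of the patients themselves".

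Table 1 places the Working Alliance Inventory (WAI) at T2 only, attachment at T1 and T3, and pain and the Oswestry Disability Index (ODI) at T1, T2 and T3.

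**The concern.** Mediator and outcomes agree between hypothesis and analysis; the exposure does not. An analysis with attachment as exposure asks whether insecure patients do worse because they form a weaker alliance. That question concerns patients and can be put to either group alone. The hypothesis asks whether training the team improves the alliance and thereby the outcome, which only a contrast between the groups can answer.

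At stake is the mechanism that motivates the intervention. If the text is followed as written, that hypothesis goes untested although the data to test it are collected.

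**Working it through.** **Side by side**

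| | Exposure | Mediator | Outcomes |
|---|---|---|---|
| Hypothesis (Background) | Study group | Working alliance | Pain, physical functioning |
| Statistical analysis | Attachment | Working alliance | Pain, physical functioning |

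Attachment cannot stand in for group: it is assessed identically in both groups, and the article says that the intervention does not aim to change it.

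**What each exposure estimates.** The article gives no figure for the mediation analysis, so there is none to reproduce. Let G be group (0/1), A insecure attachment (0/1), M the alliance in SD units and Y the outcome:

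- M = αG·G + αA·A + αGA·G·A + error
- Y = b·M + error

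With equal groups and A balanced between them:

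- attachment as exposure: indirect effect = (αA + αGA/2)·b
- group as exposure: indirect effect = (αG + p·αGA)·b, where p is the proportion insecure

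With αGA = 0 these reduce to αA·b and αG·b. The first does not contain αG. Simulated means (N = 186, 3,000 runs, b = 0.4, p = 0.6, all assumed) agree:

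| αG | αA | Attachment as exposure | Group as exposure |
|---|---|---|---|
| 0.5 | 0 | 0.00 | 0.20 |
| 0 | −0.5 | −0.20 | 0.00 |
| 0.5 | −0.5 | −0.20 | 0.20 |
| 0 | 0 | 0.00 | 0.00 |

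Rows two and three give the same attachment-based estimate, although the training does nothing in one and works in the other.

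**Illustrative rates when the training does nothing.** Assumptions: p = 0.6, b = 0.3, unit error variances, mediation declared when both paths have p < 0.05. The 93 per group (N = 186) is from Sample size calculation.

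- SE of the attachment path = √(1/111.6 + 1/74.4) = 0.150
- SE of the alliance path = 1/√186 = 0.073; z = 0.3/0.073 = 4.09; power 0.98
- Deficit 0.2 SD: z = 1.34, power 0.27; 0.27 × 0.98 = 0.26
- Deficit 0.3 SD: z = 2.00, power 0.52; 0.52 × 0.98 = 0.51
- Deficit 0.5 SD: z = 3.34, power 0.92; 0.92 × 0.98 = 0.90

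Simulation gives about 25%, 50% and 90%. With group as exposure, the 0.5 SD case gives about 5%. At 184 and 194 patients (those who received the T1 questionnaire, from Trial status, not completers) the attachment-based rates are about 49%, 81% and 99.7%.

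**Reverse case.** If the training raises the alliance by 0.5 SD and attachment is unrelated to it, attachment as exposure declares mediation in about 5% of runs and group as exposure in about 91% (93 per group).

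**With interaction.** Suppose insecure patients are 0.5 SD lower in controls and the training removes the whole deficit (αA = −0.5, αGA = +0.5). The attachment path averages −0.25, and its rate falls from about 90% to 36%. With half the deficit removed it is about 69%. Under full repair, group as exposure reaches about 51%, and a test of the group-by-attachment interaction on the alliance about 38%.

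**The case against.** *Attachment may be shorthand for the attachment intervention.* The section Design labels the second block that way, and Statistical analysis gathers attachment style and study group under one research condition. But the same paragraph names the two as separate elements and never uses attachment alone for the group. The reading is possible but weak; if it was intended, the sentence is ambiguous and still needs correcting.

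*The attachment question is legitimate.* This stands. The Background cites evidence that insecurity impairs the alliance and psychosocial outcome. It justifies keeping the analysis as a secondary one, not using it to answer the mechanism hypothesis. Fig. 2 is not available to check which paths it draws.

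*A condensed article need not list every analysis.* This also stands. A reader might count the lack of a separate between-group WAI comparison as an error; the full plan may contain one, so it is not an error here. The exposure is different, because the article names one.

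*The harm is easily overstated.* A reader might infer that a positive result will be presented as proof that the intervention works through the alliance. Nothing in the article says so; its sentence ascribes the effect to attachment. A reader might also infer that the planned analysis tends to fail when the training succeeds. That needs an interaction, is marked only under full repair, and in that scenario the group-based tests are not strong either.

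**Conclusion.** The point holds as a mismatch between the stated hypothesis and the stated analysis. As written, the mediation analysis does not test whether the intervention acts through the working alliance. This follows from the text and the algebra. The exact equality of the attachment-based indirect effect with and without a training effect assumes no group-by-attachment interaction, and either attachment balanced between groups or adjustment for group.

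The percentages are illustrative only. The documents give no path values, and the false-attribution rate at 93 per group moves from about 25% to 90% as the assumed deficit goes from 0.2 to 0.5 SD.

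The reach is limited. A reader might infer that the main efficacy result is compromised; it is not, because the analysis of variance on pain intensity and physical functioning includes study group. Even the corrected mediation analysis supports only a cautious causal reading, since the groups are sequential and not randomised.

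**What to change.** Reword the mediation sentence in Statistical analysis along these lines: *The exposure is study group (intervention versus control), the mediator is the WAI score at T2, and the outcomes are VAS pain and ODI, adjusted for their T1 values and the planned covariates. T3 is the main time point for the mediation outcome. Mediation of the T2 outcome is also reported and described as concurrent, because the WAI is measured only at T2. The effect of study group on the WAI is estimated as part of the model. T1 attachment enters as a moderator of that path; this is exploratory, as power for the interaction is limited.*

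Keep the attachment, alliance, outcome analysis as secondary, reported by study group. If attachment was meant as shorthand for the intervention, the same rewording settles it.

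The cost is wording only. Table 1 already schedules the WAI at T2, attachment at T1 and the outcomes at all three assessments in both groups. The rewording does not remove the limits set by the single WAI assessment and the non-randomised design, and the report should state both.
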